**Figure 1 F1:**
[figure not shown]
Participant flow chart based on the Consolidated Standards of Reporting Trials guidelines.

**Figure 2 F2:**
[figure not shown]
Codesign process of the AWACAN-ED public toolkit with communities in South Africa and Zimbabwe. AWACAN-ED, African aWAreness of CANcer and Early Diagnosis.

#### The AWACAN-ED public toolkit

The toolkit consists of health communication infographics with descriptions of possible symptoms of breast, cervical or colorectal cancer as well as messages to encourage consultation with primary care providers when symptoms occur. Each set of health infographics is available in English, Afrikaans, isiXhosa, Ndebele and Shona (five languages for three sets of cancer symptoms, producing a portfolio of 15 tools, available at http://www.awacan.online). Symptoms depicted in the AWACAN-ED public toolkit were adapted from WHO guidelines^24^,^26^ and other existing cancer awareness campaign materials. Commissioned graphic designers, facilitated by members of relevant cancer organisations, including the Cancer Association of South Africa (CANSA), were involved in developing prototype infographics for feedback from community participants.

#### Delivery of intervention

The intervention will be delivered face-to-face and one person at a time by experienced fieldworkers. Participants will be asked to complete a pre-intervention questionnaire (T0) and then to interact with and review the content of a printed version of their assigned cancer infographic for about 10 min. They will receive the tool in both English and their chosen language. After exposure to the tool, participants will be invited to take a break and to watch a video for around 15 min. This short activity, not related to health, will serve as a distractor item before participants are asked to complete the post-intervention questionnaire (T1).

### Outcome measures

The preintervention (T0) assessment will include sociodemographic questions (age, gender, relationship status, education and language most spoken at home), and any previous knowledge and experience of breast, cervical or colorectal cancer among family and friends.

To evaluate the efficacy of the AWACAN-ED public toolkit, we will measure two outcomes before (T0) and at two points after the intervention (T1: 15 min after the intervention; T2: 1 month after the intervention): recall of symptoms (primary outcome) and intention to seek help (secondary outcome). See study instrument in online supplemental material 1.

To assess recall of symptoms, an open-ended question will be used: *“Please would you name as many symptoms or signs of [breast, cervical, or colorectal] cancer as you can think of?”*.^27^ Responses will be recorded verbatim and will be coded by two researchers in each country against an agreed list of symptoms from the AWACAN survey for breast (15 symptoms) and cervical (11 symptoms) cancer awareness^27^ and from the Bowel Cancer Awareness Measure (9 symptoms).^28^ Participants will score ‘1’ if they mention a symptom that corresponds to the list of symptoms, and ‘0’ if they do not mention it and summed to produce total score of the number of recalled symptoms for each cancer type.

Intention to seek help will be measured by asking participants to report how soon they would visit the pharmacy or clinic or health centre or hospital, if they noticed symptoms of possible breast, cervical and colorectal cancer^27^ with five response options (‘never’, ‘less than 1 week’, ‘between a week and 1 month’, ‘between a month and 3 months’ and ‘3 months or more’). Only women will be asked the items about seeking help for breast or cervical symptoms. For analysis, responses will be dichotomised to ‘less than 1 week’ and ‘more than 1 week’.

To assess the emotional impact of the AWACAN-ED public tools, we will measure state anxiety which is defined as a transitory emotional response to a specific situation. A measure of emotional response to cancer symptoms^29^ that has previously been used in the African context was adapted for this study. The scale contains four items on feeling anxious, distressed, concerned and afraid. The participants select from three response options (‘no, not at all’, ‘yes, a bit’, ‘yes, a lot’) which are assigned numerical values (1–3). These values are summed to calculate an anxiety score. Higher scores indicate higher levels of state anxiety. This state anxiety measure will be administered prior to the intervention (T0) and in the first postintervention questionnaire (T1).

As an indicator of acceptability, participants will be asked how engaging they found the AWACAN-ED tool across five aspects of engagement (appealing, unpleasant, interesting, hard to understand, informative) adapted from previous studies.^30 31^ Response options will include ‘agree’; ‘disagree’ and ‘don’t know’. Participants will have the opportunity to add further comments or suggestions regarding the AWACAN-ED tool. Responses will be recorded verbatim. These items will only be asked in the first postintervention questionnaire (T1).

### Sample size and data analysis plan

Participant characteristics and outcomes will be summarised using descriptive statistics, including mean and median, SD and IQR. To assess how engaging participants found the health communication tools, we will use descriptive statistics to report the proportion of participants who agreed with each aspect of engagement. For the open response question, two researchers will independently code the responses into thematic categories.

We have estimated the sample size based on the assumption that the baseline number of expected recalled symptoms before the intervention will be equivalent to the average number of breast cancer symptoms recalled in South Africa using the same measure.^32^ The expected effect of the intervention on symptom recall was assumed to match or exceed the increase observed in a comparable study of lung cancer symptom recall in the UK^33^ that had a more conservative impact than a recent quasi-experimental study in South Africa.^34^ Based on these assumptions, a sample size calculation for a paired t-test with a significance level (α) of 0.05 and a power of 80% resulted in an estimated requirement of 144 participants per intervention group (N=432). This will be distributed across the two settings in South Africa and two in Zimbabwe (see table 1). To allow subgroup analyses by gender, age band and language, we will recruit at least 20 participants to each category and recruit twice as many women (n=288) as men (n=144). We anticipate minimal missing data as the questionnaires will be administered by experienced fieldworkers and researchers. However, listwise deletion will be used if any data is missing at random. Statistical analyses will be conducted using R software (2021).^35^

**Table 1 T1:** Planned minimum sample sizes required and distribution by intervention group

Research site	Intervention groups			Total
	Breast cancer tool	Cervical cancer tool	Colorectal cancer tool	
South Africa (Western Cape)				
Urban	36	36	36	108
Rural	36	36	36	108
Zimbabwe (Harare)				
Urban	36	36	36	108
Rural	36	36	36	108
Total	144	144	144	432

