### Randomisation, intervention allocation and blinding

After consent is obtained, participants will be asked to complete a preintervention survey in their chosen language (English, Afrikaans, isiXhosa, Ndebele and Shona), including sociodemographics and any previous experience of breast, cervical and colorectal cancer among family and friends. Participants will then be randomly assigned to the exposure to one of the three (allocation ratio 1:1:1) cancer infographic tools (either breast, cervical or colorectal cancer). There will not be a ‘no intervention’ control group: each participant will only be exposed to one cancer tool and will act as the control group for the two other cancer tools.^22^ We have not included a ‘no intervention’ control group due to ethical concerns of withholding information about cancer symptoms to communities who are known to lack access to information and have low cancer awareness, but also due to the likelihood of participant demoralisation and attrition for taking part in a study but receiving no intervention. However, it is acknowledged that this prevents insight into the impact of multiple completions of the same survey. Simple randomisation techniques will be used in each of the four study settings using an online randomisation service (eg, www.sealedenvelope.com) (see study flow chart in figure 1). Due to the overt nature of the intervention, blinding participants and fieldworkers will not be possible, but data analysts will be blind to group and the allocation sequence will be concealed from the person allocating participants to the interventions using sealed opaque envelopes.

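### The only inferential method named is a paired t-test, used for sizing; it takes T0 recall only by subtraction and leaves out the other-tool arms that serve as controls, so a baseline-adjusted between-arm model should be stated

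*Protocol article*

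**What the plan says.** All references are to the protocol article.

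- **Outcome measures.** For recall of symptoms (primary) and intention to seek help, "we will measure two outcomes before (T0) and at two points after the intervention". Every participant therefore has a T0 recall score, a score at 15 minutes (T1) and a score at 1 month (T2).
- **Randomisation, intervention allocation and blinding.** Allocation is 1:1:1 to the breast, cervical or colorectal tool. There is no untreated arm; each participant serves as a control for the two tools not received. "Simple randomisation techniques will be used in each of the four study settings".
- **Sample size and data analysis plan.** The size comes from "a sample size calculation for a paired t-test with a significance level (α) of 0.05 and a power of 80" per cent, which "resulted in an estimated requirement of 144 participants per intervention group (N=432"). Table 1 spreads this as 36 per arm in each of four settings. Baseline recall is taken as "equivalent to the average number of breast cancer symptoms recalled in South Africa using the same measure", and the effect "was assumed to match or exceed the increase observed in a comparable study of lung cancer symptom recall in the UK". Neither is given as a number, and no SD or correlation is given. The rest of the section covers descriptive statistics, subgroups, missing data and software. No other inferential method is named.

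**The concern.** The design asks whether people shown a given tool recall more symptoms of that cancer than people shown a different tool. A paired t-test asks whether recall rises from T0 within one arm. It does not use the controls, so it cannot separate the effect of the tool from the effect of answering the same survey twice. The article itself acknowledges that it has no untreated group with which to study repeat completion.

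A second issue remains once the arms are compared. If the paired logic is carried over as a comparison of raw changes, T0 recall enters with its slope fixed at 1. When the true slope is below 1, as regression to the mean in a symptom count would suggest, subtraction over-corrects a chance baseline difference and usually wastes precision. Allocation within setting is unrestricted, so such chance differences can occur. At stake is precision on the primary outcome from data already being collected.

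**Working it through.** **Inputs from the article.** 144 per group; alpha 0.05 (sidedness not stated, two-sided assumed); power 80%; each tool's controls are the other two arms, so 144 v 288.

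**Assumptions, because the article gives no figures.** Correlation rho between T0 and post-intervention recall, varied from 0.3 to 0.9; equal SDs at T0 and follow-up, relaxed in step 4; no change in the other-tool arms.

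**Step 1: the plan's own figure.** The 144 cannot be reproduced forward without a mean change and its SD. Solved backwards with the noncentral t (143 df), 80% power at n = 144 needs a standardised change dz = 0.235. The normal approximation is (1.960 + 0.842)/√144 = 0.2335. One-sided, dz would be 0.208.

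**Step 2: raw change compared between arms, same dz.** The noncentrality is dz/√(1/144 + 1/288) = 0.235/0.1021 = 2.30, giving 63.2% power. Pairwise, 144 v 144, it is 0.235/0.1179 = 1.99, giving 51.1%. To reach 80% on raw change would take 214 in the own-tool group against twice as many controls, or 285 per arm pairwise.

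**Step 3: adjusting for T0 recall, equal SDs.** In units of the cross-sectional SD, the effect is dz·√(2(1−rho)) and the adjusted residual SD is √(1−rho²). The variance ratio of adjusted to raw-change analysis is therefore (1−rho²)/(2(1−rho)) = (1+rho)/2, and the effective standardised effect is dz/√((1+rho)/2).

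| rho | Effective effect | Raw change, 144 v 288 | T0-adjusted | Gain (points) |
|---|---|---|---|---|
| 0.3 | 0.292 | 63.2% | 81.3% | 18 |
| 0.5 | 0.271 | 63.2% | 75.6% | 12 |
| 0.7 | 0.255 | 63.2% | 70.3% | 7 |
| 0.9 | 0.241 | 63.2% | 65.5% | 2 |

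For 144 v 144 at rho 0.5 the figures are 51.1% and 63.1%, also a gain of 12 points.

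**Step 4: unequal SDs.** Let the follow-up SD be k times the T0 SD. The change SD is √(1 + k² − 2k·rho) and the adjusted residual SD is k√(1−rho²). With k = 1.3 and rho 0.5 these are 1.179 and 1.126, so the effective effect is 0.235 × 1.179/1.126 = 0.246 and power is 67.2%, a gain of 4 points. At rho 0.3 the gain is about 9 points, and at 0.7 it is close to nil.

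**Step 5: setting.** Steps 2 to 4 contain no setting term. If setting explains 5% or 10% of residual variance (assumed), the adjusted power at rho 0.5 rises from 75.6% to about 78% or 80%, a further 2 to 4 points.

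**The case against.** The strongest objection is that the paired t-test is cited for the sample size and nothing more. The article does not say that recall will be analysed that way, that raw change will be compared between arms, or that baseline and setting will be left out. Covariates are commonly left to a full protocol or SAP, and neither is shown. This stands: omission of adjustment from the trial's analysis is not established. What remains is that the article does fix a basis for 144 per group, and that basis uses neither the control arms nor T0 recall as a covariate.

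Three stronger readings are tempting and are not supported:

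- **That the named test loses 12 points of power.** It does not. The paired test has its planned 80% for the within-arm question. The 12 points belong to a between-arm comparison of raw change, which the article never names, and only at an assumed rho of 0.5 with equal SDs.
- **That ignoring setting causes the loss.** The gains in the table come entirely from T0 adjustment. Differencing already removes constant differences in recall between settings, so a change-score analysis leaves only setting differences in change.
- **That leaving out the strata makes standard errors too wide.** That argument needs allocation that forces balance within strata. The article specifies simple randomisation in each setting, under which the unadjusted standard error is right for the unadjusted estimate.

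It is also fair to say that a between-arm comparison of raw change is valid under randomisation. The case for adjustment is precision and the handling of chance imbalance, not bias.

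**Conclusion.** The point holds in a limited form. The only inferential method named, and the basis of the sample size, does not match the comparison the design sets up, and it uses baseline recall in a way that is usually less efficient. At the effect implied by 144 per group, a 144 v 288 comparison of raw change has about 63% power. T0 adjustment recovers roughly 2 to 18 points over rho 0.9 to 0.3 with equal SDs, and about 0 to 9 points if the follow-up SD is 1.3 times baseline. No single figure can be given, because the article reports no effect size, SD or correlation. Adjusting for setting is worth having because it follows how allocation was run, but its contribution to power is small. This should be changed; it does not invalidate the trial.

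**What to change.** State the primary analysis of each cancer's recall score as a linear model of post-intervention recall (T1, and T2 likewise) on tool group, own tool versus other tools. Include T0 recall of the same cancer and study setting (four levels) as covariates, with robust standard errors because the score is a count. Keep the paired t-test as a description of within-arm change. If the full protocol or SAP already contains such a model, bring the article's section on sample size and data analysis into line with it, and give the effect size, SD and correlation assumed so that between-arm power can be checked.

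The cost is wording. T0 recall and setting are already collected, no participants are added, and the four covariate terms (T0 recall and three for setting) are negligible against 432 participants. Recruitment began in July 2025 with completion due by June 2026, so the model should be fixed before outcome data are analysed and reported to the registry, as the article already provides for protocol modifications.

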## Methods and analysis

### Study design

The AWACAN-ED public toolkit study is a three-arm parallel-group randomised controlled multisite, community superiority trial. The study protocol reports in adherence with the Standard Protocol Items: Recommendations for Interventional Trials guideline.^18^,^20^ The main hypotheses of this randomised control trial (RCT) are that the exposure to the AWACAN-ED public tool will improve the recall of symptoms of breast, cervical and colorectal cancer and enhance the intention to seek timely help for symptoms of possible cancer, without increasing anxiety.

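### The 80% power is for a before-after paired t-test within one arm, not for the randomised comparison between arms

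*Protocol article*

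**What the plan says.** Under Study design, the trial is a "three-arm parallel-group randomised controlled multisite, community superiority trial". Under Randomisation, intervention allocation and blinding, allocation is 1:1:1 with no untreated group, and "each participant will only be exposed to one cancer tool and will act as the control group for the two other cancer tools". The same section adds that "it is acknowledged that this prevents insight into the impact of multiple completions of the same survey".

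Under Sample size and data analysis plan, the number per arm comes from "a sample size calculation for a paired t-test with a significance level (α) of 0.05 and a power of 80" per cent. The result is 144 in each of three arms, 432 in all. The inputs are described but not given as numbers. Baseline recall is taken as "equivalent to the average number of breast cancer symptoms recalled in South Africa using the same measure", and the effect "was assumed to match or exceed the increase observed in a comparable study of lung cancer symptom recall in the UK". The article gives no SD, pre-post correlation or sidedness, and no expected change in the control arms. The paired t-test is the only inferential test it names.

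**The concern.** The design and the sizing answer different questions. The design asks whether people shown a given cancer's tool recall more of that cancer's symptoms than people shown another tool. The sizing asks whether recall in one arm rises from its own baseline. Nothing about the control arms enters the calculation, so its 80% cannot be read as the chance of detecting a difference between randomised groups.

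This is the article's only power statement, and it concerns the primary outcome. A reader will take it as the power of the randomised trial. If the paired test also became the main analysis, any rise from being asked the same question again would count as an effect of the tool, and the randomisation would play no part in the inference.

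**Working it through.** **Inputs.** From the article: 144 per arm, three arms, alpha 0.05, power 80%, and the other two arms as control (288). Assumed here: a two-sided test, equal SDs across arms, each cancer's recall asked in every arm (as the control role requires), and the correlations and control gains shown below. All powers use the noncentral t distribution.

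**Step 1: the plan's own figure.** Without an effect size or SD, 144 cannot be reproduced forwards. It can be back-solved. Let dz be the mean change divided by the SD of change. A paired test with n=144 has noncentrality dz × √144 = 12 dz, and 80% power at two-sided 0.05 needs dz = 0.235 (normal approximation 0.233). If the test was one-sided, dz = 0.208.

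**Step 2: the same effect as a between-arm comparison of change.** The noncentrality is dz × √(n1·n2/(n1+n2)).
- 144 v 288: 0.235 × √96 = 2.30, power about 63%.
- 144 v 144: 0.235 × √72 = 1.99, power about 51%.

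The variance factor is 1/144 for the paired test and 1/144 + 1/288 for the pooled contrast, which is 1.5 times larger. For scale, 80% power on change scores against both other arms would need about 214 per arm.

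**Step 3: the same effect with baseline adjustment, 144 v 288.** The SD of change is σ√(2(1−ρ)) and the ANCOVA residual SD is σ√(1−ρ²). The effect in residual SD units is therefore dz × √(2/(1+ρ)), where ρ is the T0-T1 correlation.

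| ρ (assumed) | Power, controls do not gain | Power, controls share a quarter of the rise |
|---|---|---|
| 0.3 | 81% | 57% |
| 0.5 | 76% | 51% |
| 0.7 | 70% | 46% |

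Relative to the paired test, the squared standard error is 1.5(1−ρ²) / (2(1−ρ)) = 0.75(1+ρ). This is below 1 when ρ is under 1/3. The adjusted contrast therefore matches or beats the paired test's power only for ρ of about 1/3 or less, and only if controls do not gain.

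**Step 4: a conditional check on validity.** Suppose the paired test were the primary analysis and a tool did nothing, but repeat questioning raised recall by 0.10 or 0.20 SD of change. The noncentrality would be 1.2 or 2.4, and the test would be significant about 22% or 66% of the time instead of 5%. The size of any such rise is an assumption; the article gives none.

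**The case against.** Four points can be made for the plan.

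- **The paired test is named only for sizing.** A reader might infer that it is the planned primary analysis and that the trial will credit repeat-questioning gains to the tools. The article does not say so. Its cross-arm control statement points the other way, and a fuller analysis plan may specify a between-arm model. This stands, and Step 4 is therefore conditional. It does not rescue the power statement, which would not apply to such a model.
- **The trial may still have 80% power.** A reader might infer that it is underpowered, or that 144 was miscalculated. Neither is shown. With baseline adjustment, a low correlation and no control gain, the randomised contrast reaches 80%. The assumed increase is also described as one to be matched or exceeded, so the true effect could be larger. This stands: the power of the contrast is unstated, and the size of any shortfall is not fixed.
- **The figures rest on a back-solved effect.** They do, because the article supplies no numbers. The mismatch between the sizing test and the design does not depend on them.
- **The caveat about repeat survey completion is defensible.** A reader might infer that it is simply wrong, because the other arms answer the same recall item repeatedly. Those arms also study a cancer infographic, however, so their change is repeat questioning plus any spillover. They do not isolate the repeat-survey effect. They do control for it in the between-arm contrast, which the caveat leaves out.

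**Conclusion.** The point holds as a mismatch. The only stated power belongs to a within-arm change, while the design makes a between-arm comparison of 144 with 288. If the planners' effect is the back-solved 0.235, power for the randomised contrast is about 63% on change scores and about 70% to 81% by ANCOVA for correlations of 0.7 down to 0.3. The ANCOVA range falls to 46% to 57% if controls share a quarter of the rise. These figures assume a two-sided test, equal SDs, complete data and, except for the last range, no control gain. They show how far the power could move; they are not estimates of the trial's actual power. The conclusion that the power statement needs replacing does not rest on them.

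**What to change.** - For each cancer's recall, state the primary analysis as the arm given that cancer's tool against the other two arms pooled, adjusted for T0 recall and study setting, at one named post-intervention time point (T1 or T2).
- Replace the paired-t power statement with the power or detectable difference of that contrast at N=432. Calculate it from the sponsor's own effect and SD with a stated assumed pre-post correlation, and give these inputs. The ranges above should not be adopted as the answer.
- Report within-arm change as description only.
- Qualify the remark on repeat completion: the arms not given a tool show repeat questioning plus any spillover from another cancer's tool, so the contrast controls for repeat questioning although it does not isolate it.

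The cost is wording and a possibly less favourable power figure, with no extra participants or data. The change should be made before analysis and reported to the registry, as the article already provides for protocol modifications.

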**Methods and analysis:**

A randomised, multisite, controlled community trial will evaluate a culturally tailored health infographic toolkit delivered in rural and urban settings in the Western Cape Province in South Africa and Harare and surrounding provinces in Zimbabwe. Participants will be randomised to receive one of three African aWAreness of CANcer and Early Diagnosis (AWACAN-ED) cancer awareness tools, coproduced with local communities, comprising health communication infographics with descriptions of breast, cervical and colorectal cancer symptoms plus messages to encourage consultation with primary care providers if symptoms occur, all presented in English and four local languages. We will recruit 144 participants in each of the three intervention groups (N=432). The primary outcome will be recall of symptoms and the secondary outcomes will be (1) intention to seek help, (2) emotional impact and (3) acceptability of the toolkit. Outcomes will be measured preintervention and at two points postintervention: after 15 min and 1 month.

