### Eligibility criteria and recruitment process

Participants will be eligible for the trial if they are at least 18 years old and reside in the selected study areas. Participants will be excluded if they fulfil any of the following exclusion criteria:

Previous self-reported diagnosis of breast, cervical or colorectal cancer.Unable to communicate in English, Afrikaans, isiXhosa, Ndebele or Shona.Unable to provide informed consent.

The sample will be recruited in community-based sites, such as community centres, churches and at local events, with the assistance of members of the community advisory boards in the Western Cape (South Africa) and Harare and surrounding provinces (Zimbabwe). Previous AWACAN-ED health facility assessments informed the selection of these areas, which represent rural and urban communities and are comparable in size and population. Experienced field workers will approach potential participants, check eligibility, invite them to participate in the study and gain written informed consent. Both women and men will be included, but we will recruit more women than men (ratio 2:1). The inclusion of men in the evaluation of the cervical and breast cancer tools responds to the important role that male partners play in women’s help-seeking behaviour for cancer reported in the literature^21^ and was emphasised during our community workshops. Recruitment will last up to 6 months.

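### Enrolment equals the number the power calculation requires and incomplete cases are deleted, so the stated 80% power has essentially no margin for loss by the 1-month follow-up

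*Protocol article*

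**What the plan says.** The sample size section of the protocol article bases the trial on "a sample size calculation for a paired t-test" with "a significance level (α) of 0.05 and a power of 80"%, which "resulted in an estimated requirement of 144 participants per intervention group (N=432").

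The recruitment figures all match that requirement:
- The abstract states: "We will recruit 144 participants in each of the three intervention groups (N=432").
- The sample size section will "recruit twice as many women (n=288) as men (n=144"), which again sums to 432.
- Table 1 has 36 participants per group in each of four settings, so 144 per group. Its title describes these as planned minimum numbers. No larger target is given.

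Under Outcome measures, recall is the primary outcome. It is taken before exposure (T0), 15 minutes after it (T1) and again at "T2: 1 month after the intervention".

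On missing data the sample size section says: "We anticipate minimal missing data as the questionnaires will be administered by experienced fieldworkers and researchers". It then prescribes listwise deletion for data missing at random. On where participants come from, the eligibility section says: "The sample will be recruited in community-based sites, such as community centres, churches and at local events".

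**The concern.** A paired test uses only people measured at both times. If 144 pairs are needed and 144 people are enrolled, each person lost before the second measurement takes the analysis below the number behind the 80%. At T1 this matters little, because T0, exposure, a 15-minute break and T1 follow one another. T2 is different: people recruited at community venues have to be reached again a month later.

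The one reason offered for expecting little missing data concerns how the questionnaires are administered. That bears on skipped questions, not on absent people. The sample size section therefore gives a reason for ignoring one kind of loss and applies it to both.

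T2 is the trial's only evidence that recall lasts beyond the session. If a non-significant change at T2 is read against a nominal 80% power, lost precision may be mistaken for fading recall.

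**Working it through.** **Inputs from the document.** Paired t-test; α = 0.05; power 80%; requirement 144 per group; enrolment 144 per group (36 × 4 = 144; 144 × 3 = 432; 288 + 144 = 432); listwise deletion; recall at T0, T1 and T2.

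**Inputs not in the document, taken as assumptions.** A two-sided test; loss rates of 5% to 30%; and a T2 effect equal to the effect used for sizing.

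**Step 1: reproduce the 144.** This cannot be done forwards, because the article prints no mean change, SD of change or standardised effect. It can be inverted. With d the mean change divided by the SD of the change, the power of a two-sided paired t-test with n pairs is

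P(|T| > t(0.975, n−1)), where T is noncentral t with n−1 degrees of freedom and noncentrality d√n.

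Setting n = 144 and power = 0.80 gives d = 0.235 (noncentrality 0.235 × 12 = 2.82). The normal approximation, (1.960 + 0.842)/√144, gives 0.233. A one-sided test would give d = 0.208.

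**Step 2: hold d at 0.235 and remove the lost pairs.** Pairs analysed are 144 × (1 − loss), rounded.

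| Assumed loss by T2 | Pairs per group | Power (two-sided) | d detectable at 80% power |
|---|---|---|---|
| 0% | 144 | 80.0% | 0.235 |
| 5% | 137 | 78.0% | 0.241 |
| 10% | 130 | 75.8% | 0.248 |
| 15% | 122 | 73.1% | 0.256 |
| 20% | 115 | 70.5% | 0.263 |
| 30% | 101 | 64.8% | 0.281 |

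A one-sided test with d = 0.208 gives 78.2% at 5% loss, 76.3% at 10%, 71.7% at 20% and 66.8% at 30%, so sidedness hardly changes the picture.

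**Step 3: look for a margin inside 144.** If 144 is the smallest whole number that reaches 80%, power at 144 is at most 80.3%. If the calculation gave 141 and was rounded up to split evenly over four settings, power at 144 is at most 81.1%, which leaves room for about 3 losses per group. Either way the margin is close to nil.

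**Step 4: the reach of listwise deletion.** The article does not say whether a case must be complete at all three times or only at the two times being compared. If all three are required, someone missing at T2 is also removed from the T0–T1 comparison, and the table then applies to that contrast too.

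**Step 5: for reference only.** Enrolment that would leave 144 complete pairs is 144/(1 − loss): 152 per group (456 in total) at 5%, 160 (480) at 10% and 180 (540) at 20%.

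**The case against.** The strongest reply is that the article never says the 80% applies at 1 month. It gives one calculation and attaches it to no time point. A reader might infer that the plan claims 80% power at T2 and that the claim is false. The text does not support that reading: no printed figure is wrong, and what is unclear is which contrast was powered. The opposite inference, that the 80% is secure for T0–T1 and only T2 suffers, is not supported either, because deletion across all three times would reduce T0–T1 as well.

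Other points on this side:
- **Table 1 calls the numbers a minimum.** So it is too strong to say that exactly 144 will be recruited. But a minimum commits to no surplus, and the abstract gives 144 as the number to be recruited.
- **Retention has had some thought.** The randomisation section cites attrition as one reason for having no untreated arm, and the ethics section pays participants once data collection is complete. Both may help, although the article does not say whether payment follows T1 or T2. Neither is a retention assumption.
- **The effect may be larger than assumed.** The plan expects it to match or exceed a benchmark described as conservative, so actual power could stay above 80% despite losses. It could equally be lower if recall fades by 1 month.
- **This is a condensed article.** A numerical attrition rate may stand in the full protocol, and its absence here is not the point. The point rests on what the article does state: a requirement, an equal recruitment number, a deletion rule, and a reason that does not cover non-return.

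The first two bullets and the missing time point narrow the concern. They do not remove it.

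**Conclusion.** The concern holds in a limited form. On the article's own figures the 80% power needs 144 analysed pairs per group, recruitment is committed only to that number, and incomplete cases are deleted. The stated power therefore has essentially no margin for loss by 1 month, and the reason given for expecting little missing data does not address that loss.

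The size is modest at low loss, about 2 percentage points at 5%, and grows to about 4 points at 10% and 9 to 10 points at 20%. These figures rest on a back-solved effect, a two-sided test, assumed loss rates and an unchanged effect at T2. They show the scale of the problem and are not the sponsor's power at T2, which cannot be computed from the article. The point merits a correction to the text; it does not show that the trial is too small.

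**What to change.** Keep N=432 and amend the sample size section as follows:
1. State which contrast, T0–T1 or T0–T2, the 80% refers to, and that it holds only with 144 analysed pairs per group. Only the sponsor can say which was intended.
2. Give the T2 power, or the change detectable at 80% power, at the expected 1-month retention. Compute it from the sponsor's own effect and SD, not from the back-solved 0.235.
3. Apply deletion separately for each contrast, so that someone missing at T2 still contributes to T0–T1.
4. Replace the single sentence on missing data with two: one on item non-response, where the fieldworker argument applies, and one on loss to the 1-month follow-up.

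The cost is wording and one recalculation, with no extra participants. The downside is a slightly less favourable stated power for the 1-month outcome.
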